## Abstract

**Background:**

In patients with stable coronary artery disease (CAD), decisions regarding revascularisation are primarily driven by the severity and extent of coronary luminal stenoses as determined by invasive coronary angiography. More recently, revascularisation decisions based on invasive fractional flow reserve (FFR) have shown improved event free survival. Cardiovascular magnetic resonance (CMR) perfusion imaging has been shown to be non-inferior to nuclear perfusion imaging in a multi-centre setting and superior in a single centre trial. In addition, it is similar to invasively determined FFR and therefore has the potential to become the non-invasive test of choice to determine need for revascularisation.

**Trial design:**

The MR-INFORM study is a prospective, multi-centre, randomised controlled non-inferiority, outcome trial. The objective is to compare the efficacy of two investigative strategies for the management of patients with suspected CAD. Patients presenting with stable angina are randomised into two groups: 1) The FFR-INFORMED group has subsequent management decisions guided by coronary angiography and fractional flow reserve measurements. 2) The MR-INFORMED group has decisions guided by stress perfusion CMR. The primary end-point will be the occurrence of major adverse cardiac events (death, myocardial infarction and repeat revascularisation) at one year. Clinical trials.gov identifier NCT01236807.

**Conclusion:**

MR INFORM will assess whether an initial strategy of CMR perfusion is non-inferior to invasive angiography supplemented by FFR measurements to guide the management of patients with stable coronary artery disease. Non-inferiority of CMR perfusion imaging to the current invasive reference standard (FFR) would establish CMR perfusion imaging as an attractive non-invasive alternative to current diagnostic pathways.

## Background

Over the last few years, there have been a number of landmark trials questioning previously accepted management strategies for patients with stable coronary artery disease. The COURAGE [1] trial has shown no benefit of routine revascularisation both in terms of prognosis and long term symptom relief in patients with stable angina. However, subgroup analysis of the COURAGE data [2], suggests that the prognosis of patients receiving optimal medical therapy (OMT) alone or percutaneous coronary intervention (PCI) and OMT is correlated to their ischaemic burden and the amount of ischaemia reduction achieved by therapy, as assessed by single-photon emission computed tomography (SPECT). The assessment of prognosis, however, was exploratory, and not associated with outcome when adjusted for treatment.

There is evidence that the presence of stress-induced myocardial perfusion defects identified by non-invasive imaging tests such as SPECT have prognostic significance [3]. An observational study of 10 627 patients with stable angina and evidence of ischaemia as measured by SPECT described a survival advantage for revascularisation (of which 52% was PCI) over medical therapy in patients with ischaemia of more than 10% of the myocardium [4]. An alternative approach is the use of invasive fractional flow reserve (FFR) measurements to assess the functional significance of coronary stenoses. The FAME [5] and DEFER [6] trials have demonstrated that patients in whom angioplasty is only performed on FFR positive stenoses have an improved outcome compared to those patients in whom the revascularisation decision is based on a visual estimate of angiographic severity alone. The 2-year follow-up of the FAME patients showed a significant reduction in major cardiac events (MACE) in patients guided by FFR. Thus, there is accumulating evidence dictating a shift away from a purely anatomical assessment for coronary artery disease to a functional assessment. These data are of specific importance as most studies so far have determined diagnostic accuracy, whereas FAME and DEFER are among the few studies, where different diagnostic strategies were used to guide further management and thus improve outcome.

Cardiovascular magnetic resonance (CMR) perfusion is a well-established, non-invasive test with excellent accuracy for the detection of coronary artery stenoses [7] as well as abnormal FFR [8,9]. Multicentre data has demonstrated non-inferiority of CMR myocardial perfusion imaging in comparison to SPECT for the assessment of myocardial ischaemia [10]. In a recent single centre study of 750 patients the superiority of CMR perfusion in comparison to SPECT was shown mainly due to improved sensitivity (86.1% vs 65.5%) [11]. In addition, patients with a negative perfusion scan have a low likelihood (< 1%) of a major cardiac event over the following two years [12-14]. Thus, CMR perfusion seems well suited to guide the management of patients with stable coronary artery disease similar to invasive FFR measurements [15].

Although treatment decisions are increasingly being based on the combination of symptoms and objective proof of ischaemia, there is insufficient evidence on the best management strategy for patients with stable angina [16] and comparative effectiveness. The aim of the MR-INFORM study, therefore, is to establish whether guiding the management of patients with a moderate to high risk of coronary artery disease by CMR perfusion is non-inferior to guiding the management of these patients by invasive angiography and FFR.

## Methods

### Hypothesis

The principal hypothesis is that selecting patients with stable angina for revascularisation and optimal medical therapy (OMT) or OMT alone based on CMR myocardial perfusion is non-inferior to selecting patients based on routine coronary angiography and fractional flow reserve (FFR) in terms of subsequent major adverse cardiac events.

### Endpoints

#### Primary endpoint

The primary endpoint is the occurrence of a Major Adverse Cardiac Event (MACE) at one year. This is a composite end-point of death, myocardial infarction, and repeat target vessel revascularisation. See Table 1 for detailed definitions of endpoints.

**Table 1 T1:** Detailed definition of end-points

**End Point**		**Definition**
Death		All cause mortality
Myocardial Infarction	Spontaneous	Elevation of CK or Troponin above baseline with symptoms of ischaemia, ECG changes or imaging evidence of loss of myocardium [22]
	Peri-procedural	CKMB > 3x ULN - upper limit of normal (post PCI 12-24 hrs) CKMB > 5x ULN (post CABG 24-72 hours) plus new Q waves or LBBB, new native vessel or graft occlusion, imaging evidence of loss of viable myocardium [22]
Repeat revascularisation		Repeat PCI or CABG of the target lesion performed for restenosis or other complication of the target lesion (from 5 mm proximal to 5 mm distal to the stent) [23]

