### FFR INFORMED group

Within the FFR-INFORMED group, the baseline CMR scan is blinded. This scan is not used to guide further management but will provide valuable additional scientific data that will be used in analyses specific to the substudies (described below). All patients in this group are examined with invasive angiography, FFR is performed in all arteries > 2.5 mm with a diameter stenosis > 40%. FFR is attempted in all arteries up to a 99% stenosis, as long as patency is not compromised. Although this strategy differs from clinical practice, which tends to focus more on intermediate lesions, evidence from the FAME trial suggests that even in severe and mild stenosis the visual estimate can be inaccurate [17]. The cut-off of 40% was used to ensure that all stenoses in the intermediate group i.e 50 -70% were interrogated with the pressure wire. The results of invasive angiography and the FFR are used to guide further treatment. Any narrowing with an FFR of > 0.8 is regarded as not haemodynamically significant, whereas a narrowing with an FFR of ≤ 0.8 or a total occlusion is regarded as significant and revascularisation is indicated. The decision on the mode of revascularisation is left to the treating Cardiologist and depends on local practice. In the case of repeat revascularisation, when symptoms are ongoing, revascularisation will be guided according to either the FFR or CMR results depending on the group randomised.

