### Revascularisation

Revascularisation by either (PCI) or coronary artery bypass grafting (CABG) will be guided by the ischaemic territories identified by either FFR or CMR perfusion, depending on the randomisation group. For example, if the CMR perfusion scan demonstrates a perfusion defect in the left anterior descending (LAD) territory and angiographically a narrowing is identified in the LAD and right coronary artery (RCA), only the LAD artery will be revascularised.

In visual triple vessel disease, the FFR or CMR results will be used to guide the decision towards CABG or PCI.

If there is more than one artery that needs to be revascularised, the PCI procedure can be staged. If this occurs, follow-up will begin after the first procedure, and the endpoints will include both procedures.

Post-interventional FFR is useful but not mandated in order to keep the procedure as simple as possible.

The specific revascularisation technique, i.e. type of stents used, staging of the procedure, PCI or CABG etc. will be decided by the treating interventionalist and dictated by local guidelines. This is to reflect “real –world” practice and to acknowledge that practice varies between centres and countries. Similarly, the cardiac surgeons will decide on the type of surgical revascularisation that they will undertake.

In the case of patients who demonstrate scar and ischaemia on CMR perfusion subsequent revascularisation will be guided by areas of ischaemia alone rather than on the basis of scar.

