### Statistical considerations

#### Sample size

The sample size calculation is based on the primary endpoint of death, MI, and repeat revascularisation at one year. A 10% event rate in the FFR group and an equivalence margin of 6% were assumed based on the results of the FAME study [5]. A sample size of 826 would be required to determine the non-inferiority of aCMR guided strategy compared to an FFR guided strategy with at least 80% power. Allowing for a dropout rate of 10% a total sample size of 918 patients is necessary. The calculation was carried out using STATA 11SE.

We do anticipate that there will be crossover between groups, most likely from the CMR group to the FFR group, when patients continue to experience symptoms and the CMR scan has been reported as negative. This will be taken into consideration during the statistical analysis which will be done on a per protocol and an intention to treat basis.

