### Study limitations

In this prospective outcome trial we address an important clinical question. There is currently insufficient evidence on the comparative effectiveness of different diagnostic strategies in patients with stable coronary artery disease and therefore we believe that the results of this trial will help to inform future guidelines.

In order to achieve this objective, the trial has been designed to reflect “real-world“ medical practice as closely as possible. This is important for the translation of its results into routine clinical practice. However, inevitably this leads to some limitations in the study design.

Although we aim at optimising medical therapy in both groups, there are variations on what is deemed optimal in different health systems and the implementation of this is left to the primary care physician. We follow the UK guidelines to minimise variation as much as possible, the remaining variation reflects clinical practice.

A critical point is the inclusion of peri-procedural myocardial infarction and target lesion revascularisation in our end-point. These endpoints are frequently used in interventional trials. The occurrence of peri-procedural myocardial infarctions seems an important end-point as they are associated with adverse outcome and may reflect better guidance by one technique or the other. However, as we guide revascularisation by objective proof of ischaemia in both arms, we expect that all patients in the trial are guided towards fewer revascularisation procedures compared to angiography alone and that this will be reflected in low event rates in both arms. The rationale for using target lesion revascularisation is similar.

It is difficult to predict the frequency of crossover from one arm to another, which can be substantial (e.g. COURAGE trial). We do not anticipate a high rate of cross-over, however, the data monitoring committee will assess the occurrence of cross-over and allow for adaptation of the randomisation scheme to account for this.

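### Table 1 bounds repeat revascularisation by the stent, so on its literal wording late graft failure after index CABG is not counted; one definition that does not depend on index mode is needed

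*Protocol article*

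**What the plan says.** The Primary endpoint section of the protocol article gives the composite in prose: "This is a composite end-point of death, myocardial infarction, and repeat target vessel revascularisation". It then directs the reader on: "See Table 1 for detailed definitions of endpoints". The repeat-revascularisation row of Table 1 reads "Repeat PCI or CABG of the target lesion performed for restenosis or other complication of the target lesion (from 5 mm proximal to 5 mm", and the bracket closes by naming the stent as the reference point. Study limitations also uses the lesion wording: "A critical point is the inclusion of peri-procedural myocardial infarction and target lesion revascularisation in our end-point".

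Index treatment is not limited to stenting. The Revascularisation section states: "Revascularisation by either (PCI) or coronary artery bypass grafting (CABG) will be guided by the ischaemic territories identified by either FFR or CMR perfusion". On the choice of mode, the FFR INFORMED group section says "The decision on the mode of revascularisation is left to the treating Cardiologist and depends on local practice". For one anatomical group the Revascularisation section goes further: "In visual triple vessel disease, the FFR or CMR results will be used to guide the decision towards CABG or PCI".

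**The concern.** The detailed definition fits only one of the two permitted index treatments. Where the index treatment was a stent, Table 1 says where a repeat procedure must lie to count. Where it was CABG alone, the table gives no location and does not mention the graft.

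Two patients whose index treatment of the same vessel has failed can therefore be classified differently because of how they were first treated. The mode of treatment is chosen after randomisation, and in visual triple vessel disease the randomised test informs it, so randomisation does not guarantee balance. The arm that sends more patients to CABG could show fewer repeat revascularisations by definition, not through better guidance. Study limitations gives the possible reflection of better guidance as a reason for counting peri-procedural infarction, and says the rationale for target lesion revascularisation is similar. The component is also a secondary endpoint in its own right.

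**Working it through.** **Two records under each text**

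| Record | Table 1, literal | Prose (target vessel) |
|---|---|---|
| LAD stented at index; in-stent restenosis at 7 months; repeat PCI | Event | Event |
| LAD bypassed at index; graft failure at 7 months; PCI of the graft or native LAD; no infarction | Not an event: no stent, so no defined segment | Event, if the graft counts as part of the vessel |

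The infarction row does not close the gap. Its CABG criterion mentions graft occlusion, but only with CKMB above 5 times the upper limit of normal at 24-72 hours after surgery. Graft failure months later enters the composite only through spontaneous infarction or death.

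**The plan's own figures.** With 826/2 = 413 per arm, 10% in both arms, a 6-point margin and one-sided 0.025:

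- SE = √(2 × 0.10 × 0.90 / 413) = 0.02088.
- Power = Φ(0.06/0.02088 − 1.96) = Φ(0.914) = 0.82, consistent with the stated 80% or more.
- 826/0.9 = 918, as stated.

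The sample size is not at issue. It supplies the scale for what follows.

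**Size of the gap.** The article gives no revascularisation rate, CABG share or repeat rate after CABG. The following are assumptions:

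- 40% of each arm is revascularised.
- 5-20% of those have CABG.
- 3-8% of CABG patients need repeat revascularisation within one year.

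Results:

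- CABG patients per arm: 413 × 0.40 × (0.05 to 0.20) = 8 to 33.
- Uncounted events per arm: 8.26 × 0.03 = 0.25, up to 33.04 × 0.08 = 2.6. Divided by 413, this is 0.06 to 0.64 percentage points.
- Shift in the arm difference, if CABG share among revascularised patients differs by 10 points: 0.40 × 0.10 × (0.03 to 0.08) = 0.12 to 0.32 points. That is 0.5 to 1.3 patients in 413, or 2% to 5% of the margin.

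**Effect on the test.** Suppose the true difference equals the 6-point margin (10% against 16%) and the CMR arm has more CABG, so that b points are hidden. The chance of declaring non-inferiority is Φ(b/SE − 1.96), with SE = √[(0.10 × 0.90 + p(1 − p))/413] and p = 0.16 − b.

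| b (points) | SE | Chance of declaring non-inferiority |
|---|---|---|
| 0 | 0.02331 | 2.5% |
| 0.12 | 0.02327 | 2.8% |
| 0.32 | 0.02320 | 3.4% |
| 0.50 | 0.02313 | 4.1% |

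If the FFR arm has more CABG, the bias runs the other way.

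**Wider range.** Let the CABG share differ by 2 to 20 points of the whole arm and let the repeat rate be 2% to 10%. The shift is then 0.02 × 0.02 = 0.04 points up to 0.20 × 0.10 = 2.0 points. The top end is remote: with 40% revascularised, a 20-point difference of the whole arm is 0.20/0.40 = half of all revascularised patients.

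**The case against.** A reader might infer that a CABG patient can never have this event. The documents do not support that without qualification. The bracket in Table 1 can be read as fixing the lesion's edges where there is a stent, not as requiring one; a later PCI of the native lesion might then count. The prose says target vessel, and if the conflict were settled that way most of the gap would close. A stent placed after CABG could in theory qualify too. These points stand, and they make this part of the vessel/lesion conflict, not a second independent defect. They do not remove the problem. The article does not say that the bracket is conditional, it names Table 1 as the detailed definition, and its limitations section also says lesion. Even on the lenient reading, graft failure is not clearly a complication of the target lesion.

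A reader might also infer that the two tests steer patients to CABG or PCI throughout. The article says so only for visual triple vessel disease. Elsewhere mode follows the treating physician and local practice, and randomisation is stratified by site. A difference in CABG use between arms is possible but not shown.

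Finally, the row cites an outside source and the article condenses a fuller protocol, either of which may cover unstented lesions. That cannot be checked here. The printed definition is nevertheless offered as the detailed one and does not fit a treatment that the same article permits.

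**Conclusion.** The point holds in a limited form. On its literal wording, Table 1 leaves a patient treated only by CABG without a segment in which repeat revascularisation can be counted, and it conflicts with the prose above it. The exclusion can differ by arm because the arm's test guides mode in visual triple vessel disease.

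The effect is probably small: about 0.1 to 0.3 points against the 6-point margin for a 10-point difference in CABG share among revascularised patients. All rates behind that figure are assumed. It is also an upper figure for those rates, since graft failures with infarction or death are already in the composite. The direction is unknown. The point merits correction because it is an avoidable, mode-dependent rule in the primary endpoint. It is not a threat to the trial's conclusion on these figures.

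**What to change.** Reconcile the Table 1 row with the prose through one definition that does not depend on index mode. For example: unplanned repeat PCI or CABG of a vessel revascularised at index (stented, balloon-treated or bypassed), including its graft, applied identically after PCI and CABG and in both arms. The word unplanned keeps a planned staged PCI, which the article allows, from being counted as a repeat.

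Adding a vessel-and-graft line for CABG patients alone would not do. A new lesion elsewhere in the treated vessel would then count after CABG but not after PCI, which creates a new asymmetry.

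Keep the target-lesion count within 5 mm of the stent as a supportive analysis. Report the index CABG share by arm, and this component by index mode and arm. Make the change together with the vessel/lesion correction.

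Cost: the component count rises somewhat and will include some new lesions in treated vessels. The design rests on "A 10% event rate in the FFR group and an equivalence margin of 6% were assumed based on the results of the FAME study", so the 10% assumption should be reread against the revised definition. The article does not list repeat-procedure details among the data collected, although repeat revascularisation is a cost item in the cost-utility analysis; check that the eCRF records vessel and graft. With 235 patients recruited at submission, the change to a primary-endpoint definition must be dated, documented and made without reference to results by arm.

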### Secondary endpoints

• Symptoms (angina score, NYHA class) within 1 year.

• Death, myocardial infarction and repeat revascularisation as individual components of MACE.

• Cost-effectiveness of a CMR vs FFR guided selection for vascularisation.

• Occurrence of new myocardial scar tissue.

• Ischaemia reduction in the FFR vs CMR group after therapy.

### Study conduct and randomisation

MR-INFORM is a multi-centre, randomised controlled, non-inferiority trial. It is actively recruiting within the UK, Germany and Portugal. The study is performed in accordance with the principles of the Declaration of Helsinki; with all patients providing informed written consent prior to testing. The study protocol and other relevant documentation have been approved by the South London Ethics Committee (UK) and the relevant national ethics committees as well as registered on ClinicalTrials.gov identifier: NCT01236807: (http://clinicaltrials.gov/ct2/show/NCT01236807?term = MR + INFORM&rank = 1). Suitable patients are identified in the outpatient clinics and from the angiography and CMR waiting lists of the recruiting centres. If they meet the inclusion criteria and none of the exclusion criteria and provide written informed consent, they are enrolled into the study.

Patients are electronically randomised prior to the baseline CMR scan via a web-based randomisation service into randomly varying block sizes of 2 and 4, stratified by study site and gender with an allocation ratio 1:1 to MR-INFORMED or FFR- INFORMED (Figure 1).

**Figure 1 F1:**
[figure not shown]
**Study Flow diagram outlining the study design.** *CXA = Coronary Angiography.

### Patient population

Patients recruited into the study have typical symptoms of angina (Canadian Class Symptoms CCS 2-3), and either a positive exercise/bicycle test or more than two cardiovascular risk factors. Exclusion criteria include contra-indications to CMR imaging or to adenosine, poor renal function (eGFR < 30), LVEF < 30%, PCI within the last 6 months, and previous CABG. A prior myocardial infarction is not an exclusion criterion. The complete inclusion and exclusion criteria are listed in Table 2**.**

**Table 2 T2:** Inclusion and Exclusion criteria

**Inclusion criteria**	**Exclusion criteria**
CCS Class 2 and 3*AND EITHER:* 2 or more of the following risk factors (diabetes, hypertension, smoking, family history, hypercholesterolaemia) *OR* Positive Exercise treadmill/bicycle test	Contra-indications to CMR
	Contra-indications to adenosine (AV-block2 or 3, symptomatic bradycardia, COPD with evidence of bronchospasm or asthma)
	Cardiac arrhythmias which may compromise image quality, atrial fibrillation or frequent ectopic beats > 20 bpm)
Age > 18 yrs	Known Left ventricular ejection fraction of less than 30%
Willing to undergo all study procedures	Persistent CCS class 4 angina
	NYHA class 3 and 4
	Previous coronary artery bypass grafts
	PCI within the previous 6 months
	Poor renal function (GFR < 30 ml/min) and /or allergy to contrast media
	Inability to lie supine for 60 mins
	Unstable medically
	Participating in any other clinical trial
	Pregnancy / breast feeding

All patients have a baseline stress perfusion CMR scan and further management will depend on whether they have been randomised to the MR-INFORMED or the FFR-INFORMED arm of the trial. In addition, all patients receive optimal medical therapy.

